### Sample size calculation

The sample size was calculated to detect a difference in everyday memory higher than 2 points (0.5 SD) on the mean RBMT-3 score between the control and the intervention group [32]. Accepting an alpha risk of 0.05 and a beta risk of 0.1 in a bilateral contrast, and assuming a mean score of 16.07 and an SD of 4.19 [33] on the RBMT-3 in the Spanish population aged between 70 and 75 years, 75 individuals in each group will be needed. To ensure this sample size and considering an estimated rate of losses of 20 % in the EG and 40 % in the CG, the final sample size needed is 195 individuals (90 in EG and 105 people in CG, respectively).

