### Statistical analysis

Baseline comparability between the study arms will be assessed through bivariate analyses of the pre-test data set group (dependent and independent variables) comparing the control and the experimental arms. The chi-square test will be used to compare qualitative data, as well as the Student *t* test or the Mann–Whitney test for quantitative data, depending on the normality of the distribution. If differences are found in baseline characteristics, we will consider adjusting for these variables in the efficacy analysis.

A descriptive analysis will be conducted for results at baseline, at the immediate follow-up and at the delayed follow-up for the EG and CG. Categorical outcomes will be described through raw frequencies or percentages, and continuous outcomes will be described through mean scores and standard deviations. Effect measures for each outcome at the immediate and delayed follow-ups will be computed as the mean of the differences of the aggregated scores for the EG and CG. Effect measures will be presented with their 95 % confidence intervals.

The main statistical analyses to assess the efficacy of the intervention on self-perceived memory, everyday memory and executive control abilities will be performed using a repeated-measures mixed effects model for each main outcome defined in the protocol [34]. In each model, the independent variables will be the group (EG or CG), time (baseline, immediate follow-up or delayed follow-up) and any relevant characteristics that differ between the groups at the baseline assessment (e.g., age or educational level). An interaction term between time and group will be included in the analyses. The models will be fitted with the available data, ignoring missing data.

To determine whether the results have been influenced by missing data, we will conduct sensitivity analyses by fitting the models with completed datasets obtained by imputing the missing data [35]. In this analysis, missing values for the immediate or delayed post-test assessments will be imputed through the Last Observation Carried Forward (LOCF) strategy. According to this strategy, missing values will receive the value obtained by the participant in the previous assessment. In addition, we will perform sensitivity analyses restricted to those participants attending at least 80 % of the sessions.

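### Covariates are chosen by baseline comparison of randomised arms, and baseline is a response with free arm means: the interaction stays valid but loses precision, and the chosen covariates hardly change it

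*Protocol article*

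**What the plan says.** All the wording at issue is in the protocol article, Statistical analysis. The arms are first compared at baseline by chi-square, t or Mann-Whitney tests, on outcome variables as well as other characteristics. Then: "If differences are found in baseline characteristics, we will consider adjusting for these variables in the efficacy analysis".

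The efficacy model is set out two paragraphs later, one model per main outcome. Its terms are group, time with baseline as one of three levels, the group-by-time interaction, and "any relevant characteristics that differ between the groups at the baseline assessment (e.g., age or educational level". The first sentence makes adjustment optional; the second lists it as part of the model. The section names no covariate that enters whatever the baseline comparison shows, no covariate-by-time term, and no constraint that the arms share a baseline mean. The model uses available data.

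Under Baseline and follow-up assessments (text with Figure 1), the baseline assessment comes after randomisation. Description of the intervention places it before the workshops start.

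**The concern.** Two features of the stated model work against its purpose.

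- **Covariate selection.** Under concealed random allocation, a difference in a characteristic fixed before randomisation is due to chance. Its size does not show whether the characteristic predicts memory or executive scores. A strong predictor that happens to be balanced is left out, although adjusting for it could still help; a weak one that happens to differ comes in. The covariate set of each main model is known only once baseline data have been seen.
- **Baseline as a response with free arm means.** The interaction then compares raw change between arms. This subtracts the whole of a chance baseline difference, although only a fraction r of it is expected to persist. A time-constant covariate added as a main effect does not repair this.

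At stake are precision in a trial of modest size and an adjustment that does less than a reader would expect.

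**Working it through.** **Inputs from the article (Sample size calculation).** Effect: "detect a difference in everyday memory higher than 2 points (0.5 SD) on the mean RBMT-3 score". Spread: "assuming a mean score of 16.07 and an SD of 4.19". Error rates: "Accepting an alpha risk of 0.05 and a beta risk of 0.1 in a bilateral contrast". Result: "75 individuals in each group will be needed". Losses: "an estimated rate of losses of 20 % in the EG and 40 % in the CG". Recruited: 90 EG and 105 CG. Completers are therefore 90 × 0.8 = 72 and 105 × 0.6 = 63.

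**Assumed.** r is not in the article, so a range is shown. Variances are taken as equal across visits.

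**The plan's own figure.** n = 2(1.960 + 1.282)² × 4.19² / 2² = 92.2, so 93 per group. With a difference of 0.5 × 4.19 = 2.095 it is 85. The stated 75 is not reproduced; a one-sided 5% test with a 2-point difference gives 76. That is a separate matter. What counts here is that the calculation uses the raw-score SD and no r, so it does not show what power the planned change contrast has.

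**Variance of each contrast at one follow-up, complete pairs.**

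- Interaction with free baseline means: 2(1−r) × SD² × (1/72 + 1/63)
- Baseline-adjusted, or common baseline mean: (1−r²) × SD² × (1/72 + 1/63)
- Ratio, adjusted over change: (1−r²) / [2(1−r)] = (1+r)/2

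At r = 0.5 the standard errors are 4.19 × √1.00 × √(1/72 + 1/63) = 0.723 and 4.19 × √0.75 × √(1/72 + 1/63) = 0.626. Two-sided 5% t-test power for 2 points:

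| r | Variance ratio | Power, change | Power, adjusted |
|---|---|---|---|
| 0.3 | 0.65 | 64% | 82% |
| 0.5 | 0.75 | 78% | 89% |
| 0.6 | 0.80 | 87% | 93% |
| 0.7 | 0.85 | 94% | 97% |
| 0.8 | 0.90 | 99.1% | 99.6% |

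Below r = 0.5, 2(1−r) exceeds 1, so the change contrast is less precise than a plain comparison of follow-up scores.

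**Effect of a chance imbalance.** If the arms differ by d at baseline, a difference of r·d is expected at follow-up. Raw change subtracts d, leaving an error of −(1−r)d: for d = 1 point and r = 0.5, −0.5 points. Over repeated randomisations d averages zero, so there is no overall bias.

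**Effect of a covariate main effect.** The interaction is (EG follow-up − EG baseline) − (CG follow-up − CG baseline). A time-constant covariate adds the same amount to both visits of an arm and cancels. This was checked by simulation (90 against 105, three visits, equal correlations, covariance taken as known, 300 runs per setting):

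| Setting | Interaction SE, no covariate | With covariate | Common baseline mean, no covariate | Shift in interaction from the covariate |
|---|---|---|---|---|
| Complete, r = 0.5 | 0.602 | 0.602 | 0.521 | none (rounding error) |
| Complete, r = 0.7 | 0.466 | 0.466 | 0.430 | none (rounding error) |
| 20%/40% loss, r = 0.5 | 0.695 | 0.691 | 0.626 | 0.06 points on average |
| 20%/40% loss, r = 0.7 | 0.548 | 0.547 | 0.518 | 0.04 points on average |

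Under loss, the available-data model gains a little from people seen only at baseline: 0.695 against the closed-form 0.723 at r = 0.5. By normal approximation, power there is Φ(2/0.695 − 1.96) = 82% against Φ(2/0.626 − 1.96) = 89%. The closed-form gap of 78% to 89% is thus somewhat generous to the concern.

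**The case against.** **The planned analysis is valid.** A reader might infer that it is biased. It is not: simulated mean estimates lay close to the true 2 points. The loss is of precision, and at high r it is small. This stands.

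**The adjustment is not useless.** A reader might infer that covariate adjustment can do nothing here. The article says only that an interaction term is included; it does not say that its coefficient is the efficacy estimate. The effect measures are defined at each follow-up, and the sample size rests on a difference in mean score. If the estimate is the model-based group difference at follow-up, a main-effect covariate does move it. In one simulated complete data set with a 0.3 SD age imbalance, the interaction stayed at 0.392 while the follow-up difference went from 0.072 to 0.220 and its SE from 0.186 to 0.178. Even for the interaction, no change is exact only with complete data. This stands too, and limits the point to the interaction reading.

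**Power may suffice.** At r = 0.7 both contrasts exceed 90%. The Abstract gives 230 participants. Split equally (an assumption), with the same losses, that leaves 92 and 69 completers and 91.5% power for raw change at r = 0.6. So the article does not support saying that this choice leaves the trial underpowered.

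**Baseline follows randomisation.** Free baseline means have some defence if knowing the allocation, or loss before the visit, shifts baseline scores. Neither model is immune. Suppose a shift s appears at baseline only: change is biased by −s and the adjusted effect by −r·s. If the shift persists to follow-up, change is unbiased and the adjusted effect is off by (1−r)s. This calls for a stated assumption and a sensitivity analysis; it does not rule out adjustment.

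**Selection is limited.** The rule refers to relevant characteristics, gives age and education as examples, and uses no follow-up outcomes. It is therefore not a search for a favourable result, but inclusion still depends on chance imbalance.

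**Conclusion.** The point holds as one about efficiency and pre-specification. The article makes covariate adjustment depend on comparing randomised arms, and lets the arm means differ freely at baseline. Read as the group-by-time interaction, the effect is a difference in raw change, valid on average. Its variance exceeds that of a baseline-adjusted effect, which is (1+r)/2 times as large. With 72 and 63 completers, adjustment gains about 11 percentage points of power at r = 0.5, 6 at 0.6, 3 at 0.7 and almost nothing from 0.8. Main-effect covariates chosen by the stated rule leave that interaction unchanged with complete data and move it by about 0.04 to 0.06 points under the expected losses.

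These sizes rest on an assumed r, equal variances, SD 4.19, a 2-point effect and the article's loss rates. They apply to RBMT-3; the article gives no corresponding figures for the other main outcomes. They do not support a claim of bias, of an adjustment that can never act, or of a trial left underpowered by this choice.

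**What to change.** 1. Drop baseline testing as the rule for choosing covariates. Baseline characteristics can still be described by arm.
2. Name age, sex, education level and health care center as covariates in every main model, whatever the baseline differences. Age, gender and education are collected at screening, and the four centers are known.
3. Model the two follow-ups with group, time, group-by-time, the baseline value of that outcome and its interaction with time. Table 1 schedules a baseline measurement for every main outcome.
4. Say that the efficacy estimate is the adjusted group difference at each follow-up, with its 95% confidence interval.
5. State the assumption that knowledge of the allocation does not shift baseline scores. It matters most for self-rated memory.
6. Report the planned three-visit model with free baseline means as a sensitivity analysis.

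The cost is analysis wording plus the stated assumption. No new data and no change in the order of visits are needed.

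### LOCF, the only stated check on missing data, is a weak test of it when losses of 20% and 40% are expected; the main mixed model is not affected

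*Protocol article*

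**What the plan says.** Under Statistical analysis, the main analysis is a repeated-measures mixed model for each main outcome, with group, time and their interaction, fitted to the data that are available. The article then gives the sensitivity analysis a purpose, which is to find out whether missing data affected the results, and a method: "missing values for the immediate or delayed post-test assessments will be imputed through the Last Observation Carried Forward (LOCF) strategy". The carried value is that of the participant's preceding assessment. It is therefore baseline for someone who misses the immediate post-test, and the immediate post-test value for someone lost later.

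The only other sensitivity analysis keeps participants who attended at least 80% of sessions. That addresses adherence, not missing outcomes.

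The Sample size calculation section plans for unequal attrition, "considering an estimated rate of losses of 20 % in the EG and 40 % in the CG", and targets "a difference in everyday memory higher than 2 points (0.5 SD) on the mean RBMT-3 score".

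**The concern.** LOCF fixes a lost participant's change after the last visit at zero. With the planned losses, that assumption would apply to twice the proportion of controls as of EG participants. Any average change in the control arm, whether a gain from repeating the same tests or an age-related decline, is then removed to a different degree in each arm. The article itself gives reason to expect change: the workshop is meant to slow age-related memory loss, and the tests are given three times.

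Dropout may also relate to outcome, and for different reasons by arm. The withdrawal criteria include illness, accident and death, and also missing more than half of the sessions, which can happen only in the EG. Departure from missing at random is what a sensitivity analysis beside a mixed model should explore. LOCF offers one scenario, not justified in the article, and treats the filled-in values as if they had been observed. At stake is how far the trial's robustness statement can be trusted, not its main estimate.

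**Working it through.** **Inputs from Sample size calculation.** Losses are 20% (EG) and 40% (CG); the target difference is 2 points on the RBMT-3; the SD is 4.19; 90 EG and 105 CG participants are randomised.

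**The plan's own figure.** 75 × 1.2 = 90 and 75 × 1.4 = 105, total 195. Applying the stated losses leaves 90 × 0.8 = 72 and 105 × 0.6 = 63 observed, so 18 EG and 42 CG participants would have carried-forward values. The abstract gives a total of 230; the bias formula below uses only the percentages, so it does not depend on which total applies.

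**Case 1: all losses before the first post-test, unrelated to outcome.** Let c be the mean control change from baseline and d the true effect. With every visit filled in and no covariates, the group-by-time effect is the difference in mean change:

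- EG mean change under LOCF: 0.8(c + d) + 0.2 × 0
- CG mean change under LOCF: 0.6c + 0.4 × 0
- LOCF effect: 0.8(c + d) − 0.6c = 0.8d + 0.2c
- Bias: 0.8d + 0.2c − d = 0.2(c − d), which is zero only if c = d

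The article gives no value of c, so the values below are scenarios. One point is 1/4.19 = 0.24 SD. The type I error comes from a simulation with no true effect: 90 against 105 participants, SD 4.19, an assumed baseline-to-follow-up correlation of 0.6, a t test on change and 4,000 runs per row.

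| c | LOCF effect, d = 2 | LOCF effect, d = 0 | Simulated LOCF type I error |
|---|---|---|---|
| −2 | 1.2 | −0.4 | 13.0% |
| −1 | 1.4 | −0.2 | 7.8% |
| 0 | 1.6 | 0 | 5.5% |
| 1 | 1.8 | +0.2 | 7.7% |
| 2 | 2.0 | +0.4 | 14.8% |
| 3 | 2.2 | +0.6 | 23.3% |

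In the same runs, the analysis of observed changes alone was unbiased, with type I error of 4.5% to 5.1%.

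**False precision.** In the simulation with d = 2 and c = 0, LOCF estimated about 1.6 yet reached significance in 93% of runs, against 86% for the observed changes with an estimate of about 2.0. The filled-in zeros shrink the spread and restore the full sample size. An attenuated estimate can therefore still look like a firmer result.

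**Case 2: all losses after the first post-test, unrelated to outcome.** The 3-month comparison has no missing values and no bias. At 6 months, let g_E and g_C be the mean changes between the two follow-up visits. LOCF keeps 0.8g_E and 0.6g_C, so the bias is −0.2g_E + 0.4g_C. It is zero if both means are stable.

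**Case 3: half early and half late, means stable between visits.** The 6-month bias is half that of Case 1, 0.1(c − d). For d = 2 and c = 0 the estimate is 2 − 0.2 = 1.8.

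**The case against.** The strongest reply is that the main analysis is already a sound choice. A mixed model on available data is valid under missing at random, and LOCF enters only a secondary refit. This stands in full. A reader might infer that the trial's effect estimate is biased by LOCF; the article does not support that.

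Second, the timing of losses is not given. A reader might infer that most lost participants would have baseline carried forward, or that Case 1 is a lower bound on the bias. Neither follows: Cases 2 and 3 show smaller or no bias. This also stands.

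Third, the size of the bias depends on an unknown c, and at c = d there is none. A 30% shortfall (1.4 against 2) needs controls to lose a full point over the short follow-up, and nothing in the article supports that figure. This stands too, which is why the whole range is shown.

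Fourth, LOCF is not empty of information. With c = 0, the value 1.6 is the correct effect if EG dropouts truly gained nothing, so it is too small only if they would have gained the full benefit. A finding that survives this has survived one departure from missing at random. It would thus go too far to say that the check tells nothing. It remains one scenario, which the article does not justify, and it does not vary the assumption.

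Finally, an analysis plan that is not shown may add further scenarios. LOCF is the only missing-data check in this article, and no more is claimed. The article does, however, state both method and purpose, and that pairing can be judged as it stands.

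**Conclusion.** The point holds for the sensitivity analysis only. LOCF is poorly suited to the purpose that the article gives it. Under the planned losses, with early dropout unrelated to outcome, it differs from the true effect by 0.2(c − d). For a true effect of 2 points and c between −1 and 2, that is from 0.6 too small to no bias; with no true effect and c between −1 and +1, it is from −0.2 to +0.2. Later losses give a different bias, which may be smaller or zero.

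Disagreement with the main model can therefore arise from harmless dropout, and agreement gives little reassurance about outcome-dependent dropout. The algebra rests on the stated loss rates. The values of c, the timing of losses and the correlation of 0.6 in the simulation are assumptions.

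**What to change.** Replace LOCF, or keep it only as a labelled supplement, as follows:

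1. Impute missing post-test scores by multiple imputation within each arm, using baseline and observed follow-up scores, age, gender, education and, in the EG, the number of sessions attended. The article already collects all of these. By itself this step largely repeats the main model's missing-at-random assumption; it is the base for step 2.
2. Add a delta-adjusted tipping-point analysis, with shifts to dropouts' imputed values varied separately by arm. Define worse performance for each scale: lower RBMT-3, longer TMT time, more MFE failures. A uniform downward shift would improve the TMT and MFE.
3. Include the scenarios that work against the EG: EG dropouts worse, with CG dropouts unchanged or better. Making CG dropouts worse enlarges the EG advantage and does not stress a positive result.
4. Report the shift at which the conclusion changes.

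As a guide to scale, at the planned losses, EG dropouts 2 points worse on the RBMT-3 lower the difference by 0.2 × 2 = 0.4, and CG dropouts 2 points better lower it by 0.4 × 2 = 0.8. The control arm therefore deserves the closer look.

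The cost is a change of wording and a little more programming. No new data are needed, and the main analysis stays as it is. The change should be made before unblinded results are seen.

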### Ethics considerations

The participants will be informed both verbally and in writing about the aims, methods, procedures and measures performed during this study. They will also be informed about ethical issues such as confidentiality, their right to ask any questions during the study and their right to withdraw at any time. To ensure that all participants have received information about this research project and agreed to participate, all participants will be asked to sign a written consent form. The research team is committed to performing this study according to the Good Clinical Practice Guidelines of the Declaration of Helsinki. This protocol was approved by the Comitè Ètic d’Investigació Clínica (CEIC) del IDIAP Jordi Gol.

## Discussion

### Quality control

Reliability and validity are considered to be the key criteria for assessing the quality of quantitative studies. To assure these qualities, the randomization list of this randomized controlled trial will be computer-generated and will remain concealed until the participants’ assignment to each group. After the informed consent form has been signed, a study entry number will be assigned to each participant. This number will be on the outside of a closed, opaque envelope, which will allocate the participant to either the EG or the CG (single-blind allocation). Allocation concealment will prevent the occurrence of selection bias before the interventions are provided to the participants [36]. In addition, the professionals who will carry out the neurocognitive evaluations (pre-test, short-term post-test and long-term post-test) and the memory training workshop professionals will not be aware of the group to which each participant belongs.

The following procedures will also be used to guarantee the quality of the information. The intervention will be carried out by trained personnel who will follow the same protocol and materials, thus guaranteeing the homogeneity of the intervention. The same will occur with data collection, which will be conducted by specially trained professionals. Data will be collected through a specifically created data-register sheet designed by Teleform® v.10.2 software. This automated software reads scanned questionnaires and performs a validation process of the data with previously established parameters; once the data have been validated, they are entered into a specifically created dataset.

### Implications

The memory training workshop proposed in the present study could be considered as paradigmatic of the memory training interventions that are being conducted in Barcelona, even in Spain, as most of them follow the same pattern. [8, 32, 37–39]. The results of this study will be very useful for social and public health policies for older people. The findings of this study should be considered when decisions need to be made regarding investing public resources in certain interventions.

